# STUDY PROCEDURES

## Recruitment

Potential participants will be recruited through advertisements in local borough newsletters (Kensington and Chelsea and Hammersmith and Fulham boroughs), through the Royal College of Music website, through posters in communal spaces such as churches in the local area. Information about the study will also be available in local GP surgeries, mental health day centres and distributed through mental health channels such as online forums. Staff at such locations, including psychologists and psychiatrists, may be able to point service users towards the study. But it is up to the service users themselves to contact us with a view to taking part in the study. We will receive no personal information from health professionals.

## Informed Consent

Participants will personally sign and date the Informed Consent form, co-signed by a member of the research team, before any study activity is performed. Written and verbal versions of the Participant Information sheet will be presented to the participants detailing the exact nature of the study and what it will involve for the participant. It will be clearly stated that the participant is free to withdraw from the study at any time for any reason without prejudice to future care, and with no obligation to give the reason for withdrawal. The participant will be allowed time to consider whether they would like to be involved and the opportunity to ask questions to decide whether they will participate in the study.

## Potential risks and benefits

**Risks:** Participating in participatory drumming workshops involves some degree of physical movement. Participants are able to remain seated throughout, but if a participant becomes tired or finds a particular movement difficult or painful, they can sit out until they feel better. Cushions and a variety of chairs will be available to pick from. We don't anticipate that completion of surveys or provision of saliva samples will be a burden, but if it becomes so, help will be offered from a member of the research team. Participants will have to make their own way to the workshops. To minimise travel inconveniences, participants will mainly be recruited though local networks.

**Benefits:** This research aims to ascertain how musical activities can benefit mental recovery for adults with mental health conditions. So participants will benefit from being able to take part in enjoyable group activities at no cost. These activities are designed to be relaxing and there is no indication from previous studies or current communal activities that group music sessions have any adverse effects on health. The workshops may introduce participants to others who may be able to form a future support network for them; provide them with a sense of group inclusion; teach new musical skills that participants may choose to continue with after the study; and give participants a sense of personal pride in their achievements. As the sessions will be delivered by professional workshop leaders and trained musicians from the Royal College of Music, the standard of music making and teaching

will be very high.

## Screening and Eligibility Assessment

Participants will approach the study team directly if they are interested in taking part in the study. Eligibility criteria will be checked and, if eligible, participants will be sent information sheets and consent forms.

## Subsequent Assessment

The data collection carried out in week 1 will be repeated in weeks 6 and 10. For the experimental group, this will also be repeated 3 months following the end of the intervention.

## Withdrawal

If a participant withdraws from the study, data already collected with consent will be retained and used in the study. But no further data will be collected or any other research procedures carried out on or in relation to the participant.

## Definition of End of Study

The end of the study will be once participants have completed all data collection (after 10 weeks for the control group and after 10 weeks + 3 months for the experimental group).

# INTERVENTIONS

Experimental participants will take part in weekly 90-minute group drumming sessions over a period of 10 weeks. They will be split into two groups of 15-20, and sessions will run consecutively on weekday mornings in a hired community space in West London, led by a professional drummer and supported by three students from the Royal College of Music. Sessions will consist of call-and-response exercises and learning drumming patterns that build up into larger pieces. Control participants will be adults who are already taking part in regular community group social activities (e.g. quiz nights, women’s institute meetings and book clubs), but will not take part in any group musical activity during the 10 weeks.

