# STATISTICS AND ANALYSIS

## Description of Statistical Methods

Data will be analysed using IBM SPSS Version 22.0.1 (SPSS, Chicago, IL). We will compare results using repeated measures analysis of variance (ANOVAs) with planned simple contrasts, both within and between subjects. Differences with a resultant p value of <.05 will be considered significant. In the event that data is non-parametric, we will use Kruskall-Wallis one-way analysis of variance. However, if biological data is non-parametric, we will attempt to transform prior to analysing parametrically.

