## The Number of Participants

Sample size calculations using an alpha of 0.05, power of 0.8 and an effect size of 0.25 (2 groups, 3 timepoints) suggest an overall total of 28 participants will be required (14 per group). For the control group, in order to allow for drop-outs of 30%, 20 participants will be targeted for recruitment. For the experimental group, because of the range of biological markers being tested, we will match sample size with our preliminary study, and so 39 participants will be recruited. Recruitment will be continued until these targets are reached before being closed one week before the drumming starts.

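### Drumming is delivered in two shared groups, but the planned ANOVAs treat participants as independent; if changes correlate within a group, the p<.05 rule rejects too often

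*Protocol*

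**What the plan says.** Section 7 of the protocol (Interventions) has experimental participants attend "weekly 90-minute group drumming sessions over a period of 10 weeks". On delivery it says "They will be split into two groups of 15-20", with sessions "led by a professional drummer and supported by three students". Controls are people already attending various community social groups; the number and size of those groups are not given.

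Section 8.1 fixes the analysis: "We will compare results using repeated measures analysis of variance (ANOVAs) with planned simple contrasts, both within and between subjects", with p<.05 as the rule for significance and Kruskal-Wallis as the fallback. No term for drumming group appears.

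Section 8.2 sizes the study from "alpha of 0.05, power of 0.8 and an effect size of 0.25 (2 groups, 3 timepoints"), and concludes that "an overall total of 28 participants will be required (14 per group"). For controls, "in order to allow for drop-outs of 30%, 20 participants will be targeted for recruitment". For the drumming arm the reason is different: "we will match sample size with our preliminary study, and so 39 participants will be recruited". Nothing in section 8.2 allows for clustering.

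Section 6.5 (Baseline Assessments) takes saliva from the experimental group only, so cortisol and cytokines have no control comparison.

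**The concern.** Members of one drumming group spend ten weeks making music together. Section 6.3 expects the workshops to help people form supportive ties and feel part of a group. That is a route by which one member's outcome can move with another's, so some positive correlation of change within a group is plausible on the protocol's own account.

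The ANOVA takes its error term from differences between individuals. If the two drumming groups also differ from each other by chance, the uncertainty in the drumming-arm mean is larger than that error term shows. Intervals are then too short and p values too small. The between-arm HADS contrast is partly protected, because the control arm adds variance that is taken here as unaffected. A contrast from baseline within the drumming arm has no such buffer, and it is the only test the biomarkers can have.

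**Working it through.** **1. The protocol's own figure.** For the group-by-time interaction in a repeated measures ANOVA, lambda = N × f² × m/(1−rho), on (k−1)(m−1) and (N−k)(m−1) degrees of freedom. Take k = 2 arms, m = 3 timepoints, f = 0.25 and sphericity. The correlation between timepoints is not stated; rho = 0.5 is assumed.

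- N = 28: lambda = 28 × 0.0625 × 3/0.5 = 10.5 on 2 and 52 df, power 0.812. N = 26 gives 0.778.
- Dropout: 14/(1−0.30) = 20.

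The stated 28 and 20 are reproduced, on the basis of independent participants (design effect 1).

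**2. Inputs for the clustering check.** 39 drumming participants in two groups give a group size m of about 19.5; there are 20 controls. The ICC of change scores is an assumption: 0.02, 0.05 and 0.10. Controls are taken as independent.

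**3. Loss of precision.**

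- Design effect DE = 1+(m−1)ICC. With m−1 = 18.5: 1+18.5×0.02 = 1.37; 1+18.5×0.05 = 1.93; 1+18.5×0.10 = 2.85.
- Effective drumming-arm size = 39/DE: about 28, 20 and 14.
- Within-arm standard error understated by √DE: 1.17, 1.39 and 1.69.
- Between-arm standard error understated by √[(DE/39+1/20)/(1/39+1/20)]: 1.06, 1.15 and 1.28.

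**4. False-positive rate of the nominal 5% test of change.** This comes from 40,000 simulated trials per setting in the completer rows, and from a separate simulation of the same design for 39 v 20. There are two drumming groups and no true effect. The completer rows apply 30% loss to both arms.

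| Contrast | ICC 0.02 | ICC 0.05 | ICC 0.10 |
|---|---|---|---|
| Between arms, 39 v 20 | 6.2% | 8.9% | 12.8% |
| Within drumming arm, 39 | 9.2% | 16.0% | 24.9% |
| Between arms, 27 v 14 completers | 5.9% | 7.8% | 10.4% |
| Within drumming arm, 27 completers | 7.7% | 12.3% | 19.3% |

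At ICC 0 the simulated rates are about 5%.

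**5. Power at the numbers recruited.** Use the formula in step 1 with a balanced-equivalent N = 4/(1/n_eff + 1/n_control). For example, at 39 v 20 and ICC 0.05, N = 4/(1/20.3+1/20) = 40.3. Approximate power:

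| Sample | ICC 0.02 | ICC 0.05 | ICC 0.10 |
|---|---|---|---|
| 39 v 20 | 0.97 | 0.94 | 0.88 |
| 27 v 14 completers | 0.89 | 0.85 | 0.79 |

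The drumming arm keeps 14 effective participants up to ICC (39/14−1)/18.5 = 0.097 at full recruitment, and (27/14−1)/12.5 = 0.074 among completers.

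**6. Candidate corrections at 39 v 20.** Fitting arm as three fixed levels (control, drumming A, drumming B) and contrasting the mean of A and B with control gives error rates of 6.3%, 9.2% and 13.4%. That is no better than the 6.2%, 8.9% and 12.8% of the pooled model, because it moves the A–B difference out of the residual. Multiplying the drumming-arm variance by DE brings the rate back to about 5%, between arms and within the drumming arm, when the assumed ICC is the true one.

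**The case against.** The strongest objection is that the size of the error is unknown. No ICC is given, and at zero there is no problem. Both groups appear to share one venue and one leading team, and influences common to both do not create differences between them; mainly peer effects remain. For the primary HADS contrast, inflation at ICC 0.02 to 0.05 is modest: about 6% to 9%. All of this stands, and it is why the point is conditional. It does not rescue the biomarker contrasts, where an ICC of 0.05 roughly triples the error rate. Nor is this only a matter left to an SAP, because section 8.1 itself fixes the model and the significance rule.

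Three stronger readings are tempting but not supported:

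- *The study is underpowered.* A reader might infer this because the 28 assumes independence. But the plan recruits 39 v 20, not 14 v 14, and the surplus absorbs clustering across the range shown. Only among completers near ICC 0.10 does power slip just under 0.8.
- *The groups are pre-existing clusters.* Section 7 has individually recruited volunteers divided into two groups. Any correlation would come from the shared sessions.
- *The error bars are certainly too narrow.* That needs a positive ICC, which is plausible but not documented.

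Controls may cluster too, since they attend community groups. The protocol gives no basis for quantifying this. If they do, the between-arm figures above understate the inflation for a given drumming-arm ICC.

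**Conclusion.** The point holds in conditional form. The planned tests assume independence that group delivery puts in doubt. Over assumed ICCs of 0.02 to 0.10 at 39 v 20, the false-positive rate is about 6% to 13% between arms and 9% to 25% within the drumming arm. With 27 v 14 completers and ICC 0.05 it is about 8% and 12%. These figures rest on the assumed ICC, equal-sized groups and independent controls. The harm is overstated precision and false-positive risk, chiefly for cortisol and cytokines; loss of power is secondary. This is worth correcting because the remedy is cheap, but it does not undermine the design on its own.

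**What to change.** In section 8.1:

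- Record which drumming group each participant attends, and show results by group descriptively.
- For the HADS between-arm contrast and every within-arm cortisol and cytokine contrast, report the planned interval and p value. Beside them, report the same with the drumming-arm variance multiplied by 1+(m−1)ICC at ICC 0.02, 0.05 and 0.10, where m is the number per group analysed.
- Call a result robust only if it holds across that range.
- Limit the conclusion to these two groups and one leading team, and note that the controls' community groups may also cluster.

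Do not offer a three-level arm factor as the correction; step 6 shows that it leaves the error rate unchanged or slightly worse. A random effect or cluster-robust standard error is not a practical alternative either: two groups leave one degree of freedom between them, too few to estimate the ICC usefully.

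The cost is a few sentences and one extra variable. Adjusted intervals widen by the factors in step 3: at full recruitment, 1.06 to 1.28 between arms and 1.17 to 1.69 within the drumming arm. Some results may no longer fall below .05.

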# STATISTICS AND ANALYSIS

## Description of Statistical Methods

Data will be analysed using IBM SPSS Version 22.0.1 (SPSS, Chicago, IL). We will compare results using repeated measures analysis of variance (ANOVAs) with planned simple contrasts, both within and between subjects. Differences with a resultant p value of <.05 will be considered significant. In the event that data is non-parametric, we will use Kruskall-Wallis one-way analysis of variance. However, if biological data is non-parametric, we will attempt to transform prior to analysing parametrically.

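### The three-visit repeated measures ANOVA uses only participants with complete data, which sits poorly with the commitment to use withdrawn participants' data and risks completer bias

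*Protocol*

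**What the plan says.** Section 8.1 of the protocol names the software and the model: "We will compare results using repeated measures analysis of variance (ANOVAs) with planned simple contrasts, both within and between subjects", in SPSS 22.0.1. This is its only parametric analysis.

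Section 8.2 sizes the trial on two groups and three timepoints and arrives at 28 participants, 14 per group. It then adds: "For the control group, in order to allow for drop-outs of 30%, 20 participants will be targeted for recruitment". The drumming arm is set at 39 to match the preliminary study, with no drop-out rate.

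Section 6.6 repeats the week 1 data collection at weeks 6 and 10, and again three months after the intervention in the drumming arm only.

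Section 6.7 says of a participant who withdraws that "data already collected with consent will be retained and used in the study", and that nothing further will be collected.

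The protocol does not mention complete-case analysis, imputation or a mixed model.

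**The concern.** Standard repeated measures ANOVA in SPSS takes one row per person and excludes any row with a missing level. A participant with weeks 1 and 6 but no week 10 is therefore absent even from the comparison of week 6 with baseline. The same happens to someone who stays in the study but misses one visit, so the expected drop-out rate is not a ceiling on the loss.

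Two things are at stake.

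- **Use of the data.** Scores collected before withdrawal are kept under section 6.7 but do not enter the model that section 8.1 names for the primary outcome, HADS.
- **Bias.** The analysis compares completers. If leaving is related to mental state, completers differ from those who started. The study is not randomised, and its controls already attend their own social groups, so drop-out may differ between arms. Within-arm change is itself a planned result, and section 3 makes 6 versus 10 weeks a secondary objective, so a distorted week-6 result matters directly.

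**Working it through.** **1. The plan's own figures.** Inputs from section 8.2: alpha 0.05, power 0.80, effect size 0.25 (read as Cohen's f), k = 2 groups, m = 3 timepoints. The protocol gives no correlation between visits; rho = 0.5 and sphericity are assumed here.

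For the group-by-time interaction, lambda = f² × N × m / (1 − rho), with df1 = (k − 1)(m − 1) and df2 = (N − k)(m − 1).

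At N = 28: lambda = 0.0625 × 28 × 3 / 0.5 = 10.5, df = 2 and 52, power 0.81. The stated 28 is reproduced. With the drop-out allowance, 14 / (1 − 0.30) = 20, also reproduced. The sample size therefore rests on the same three-timepoint model.

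**2. How many leave the model.**

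- Controls, as documented: 20 × 0.30 = 6 lost, 14 left.
- Drumming: no rate is given. If 30% is assumed there too, 39 × 0.70 = 27.3, so about 27 are left and 12 lost.

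**3. Does power fall short?** For unequal arms, N in lambda is replaced by 4 × n1 × n2 / (n1 + n2). At rho = 0.5:

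| Controls | Drumming | Interaction power |
| --- | --- | --- |
| 14 | 14 | 0.81 |
| 14 | 27 | 0.92 (0.915) |
| 14 | 39 | 0.94 |
| 20 | 39 | 0.98 |

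At the planned correlation there is no shortfall against 0.80. For 14 v 27, power runs from 0.79 at rho = 0.3 to 0.99 at rho = 0.7.

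**4. Lost precision at week 6.** Suppose every drop-out leaves after week 6, so that all 39 + 20 have a week-6 score. The standard error ratio for the group difference in week-6 change, complete cases against everyone, is:

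- Control loss only: √[(1/39 + 1/14) / (1/39 + 1/20)] = √(0.09707 / 0.07564) = 1.13.
- 30% loss in both arms: √[(1/27 + 1/14) / (1/39 + 1/20)] = √(0.10847 / 0.07564) = 1.20.

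If some leave before week 6, less week-6 information is thrown away and both ratios shrink.

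**5. Possible bias.** Simulation of 2 million participants in one arm with no true change, unit-variance scores and higher meaning worse. Drop-out after week 6 has logit = −1 + 1 × week-6 score, about 30% lost. The slope is an assumption; the protocol offers no basis for one.

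| Correlations (wk 1–6 / 1–10 / 6–10) | Complete-case change, wk 6 | Complete-case change, wk 10 | Likelihood-based |
| --- | --- | --- | --- |
| 0.5 / 0.5 / 0.5 | −0.13 SD | 0.00 SD | about 0 |
| 0.7 / 0.7 / 0.7 | −0.08 SD | 0.00 SD | about 0 |
| 0.6 / 0.4 / 0.7 | −0.10 SD | about −0.03 SD | about 0 |

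These are within-arm shifts. If drop-out acts alike in both arms, they cancel in the group contrast: −0.13 − (−0.13) = 0.

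**6. Where the mixed model does not help.** With all correlations 0.5 and the same slope:

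- If people leave before week 6, so that the score driving drop-out is never seen, the likelihood-based week-6 change is biased by −0.20 SD, against −0.13 for complete cases. At correlation 0.7 the likelihood-based bias is −0.14.
- If drop-out depends on the unseen week-10 score, the likelihood-based week-10 bias is −0.18 SD, against −0.13 for complete cases.

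**The case against.** The strongest reply is that this is a gap, not an error. Section 8.1 names a model and never says that incomplete participants are deleted, and missing-data rules often sit in a statistical analysis plan, which is not at hand. Section 6.7 is a withdrawal clause: it promises use in the study, not in every model. Withdrawn participants' scores could still enter baseline tables, a separate comparison of week 6 with baseline, or an imputed data set. This stands to the extent that a reader who infers a flat contradiction between sections 6.7 and 8.1 goes too far; it is an unreconciled tension. But the protocol does not leave the estimator open. It fixes one whose usual SPSS form excludes incomplete rows, and sizes the trial on it.

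Other stronger readings also fail:

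- **That 30% of the whole sample is expected to be lost.** Section 8.2 gives the rate for controls only.
- **That the trial becomes underpowered.** The move from 14 to 20 controls already covers the planned loss.
- **That the treatment comparison is biased by 0.08 to 0.13 SD.** That figure is within-arm and depends on an assumed slope.
- **That a mixed model removes the bias.** It does so only when drop-out depends on observed scores, as step 6 of the working shows.
- **That the 3-month visit thins out the 10-week results.** No section adds it as a fourth level, and section 8.2 counts three timepoints.

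**Conclusion.** The concern holds in a limited form. Followed as written, the primary HADS model excludes anyone without all of weeks 1, 6 and 10, and the protocol does not square this with section 6.7. The documented loss is 6 of 20 controls; the loss among the 39 drumming participants is unknown.

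The cost in precision is a week-6 standard error larger by about 13%, or about 20% with 30% loss assumed in both arms, and in each case only if all losses come after week 6. The cost in bias is about 0.08 to 0.13 SD in within-arm week-6 change under the assumed mechanism and little at week 10. It reaches the group comparison only in so far as drop-out differs between arms, which the protocol gives no means of quantifying. Stated power is not threatened at the correlation that reproduces the plan's 28. A better method is available on the same data, so the change is worth making.

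**What to change.** In section 8.1, make the primary analysis of the week 1, 6 and 10 data a linear mixed model with group, visit and group-by-visit terms and an unstructured covariance. Use all available visits from eligible participants, and say how the section 5.2 exclusions for changes during the 10 weeks define that set. Keep the same planned contrasts: group by week 6 against baseline, and group by week 10 against baseline. Retain the complete-case repeated measures ANOVA as a sensitivity analysis. State that the 3-month data, collected in the drumming arm only, are analysed separately. Align section 8.3 with this.

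The cost is wording and slightly more analysis work. SPSS fits the model through its MIXED procedure, no new data are needed, and the unstructured covariance removes the sphericity assumption. The limitation should be stated with it: validity rests on missingness depending on observed data, so drop-out driven by unobserved scores would still bias the result.

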# SYNOPSIS

| **Study Title** | Effects of group music interventions for mental health service users on anxiety, depression, social resilience and inflammatory response | |
| --- | --- | --- |
| **Internal ref. no. / short title** | 13/LO/1811 | |
| **Study Design** | Quasi-experimental controlled study | |
| **Study Participants** | Adult mental health service users | |
| **Planned Sample Size** | Experimental: 39 to be recruited  Control: 20 to be recruited | |
| **Planned Study Period** | Recruitment from August 2014, study October 2014-December 2014 | |
|  | **Objectives** | **Endpoints** |
| **Primary** | To reduce anxiety and depression | Psychological scale:  Hospital Anxiety and Depression Scale (HADS) |

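### The between-arm HADS test pools one error variance over non-randomised arms of 39 and 20, so its 5% level holds only if the two arms vary equally

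*Protocol*

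**What the plan says.** Protocol section 8.1 names the analysis: "We will compare results using repeated measures analysis of variance (ANOVAs) with planned simple contrasts, both within and between subjects". It sets the threshold: "Differences with a resultant p value of <.05 will be considered significant". The one alternative for questionnaire data is "In the event that data is non-parametric, we will use Kruskall-Wallis one-way analysis of variance", which is triggered by the shape of the data and not by a difference in variance between arms. Section 8.3 adds only that change from baseline will be measured.

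Section 8.2 concludes that "an overall total of 28 participants will be required (14 per group"), with equal arms. It raises the control arm to 20 for 30% drop-out and sets the drumming arm at 39 to match the preliminary study, because of the biological markers. The synopsis repeats this: "Experimental: 39 to be recruited", with 20 controls. Section 6.5 takes saliva from the drumming arm only, so the markers that motivate the larger arm have no control comparison.

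Section 4 describes the design as quasi-experimental, and section 7 says: "Control participants will be adults who are already taking part in regular community group social activities". HADS is the primary outcome (sections 1 and 3). No SD is given for any scale, arm or change score.

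**The concern.** In a repeated-measures ANOVA with two groups, the group x time test and the group comparison on each simple contrast use an error term pooled over the arms. For baseline to week 10, the contrast is the ordinary pooled two-sample t test on change. Pooling weights each arm's variance by its degrees of freedom, so the larger arm dominates the estimate. The true variance of the difference in means depends most on the smaller arm. With equal arm sizes the two effects cancel. At about 2:1 they do not.

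If the smaller control arm varies more, the standard error is too small, intervals are too narrow and a true null is rejected too often. If the drumming arm varies more, the standard error is too large and power is lost. Randomisation would make the variances equal under the null of no effect. Here the controls are already settled in social activities and the drumming participants are starting a new one, so nothing in the design supplies that equality. What is at stake is the error rate of the between-arm test on the primary outcome.

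**Working it through.** **1. The plan's own figure.** The inputs in section 8.2 are "Sample size calculations using an alpha of 0.05, power of 0.8 and an effect size of 0.25 (2 groups, 3 timepoints"). For the group x time interaction, λ = f²·N·m/(1−ρ), with 2 and 2(N−2) degrees of freedom. The protocol gives no correlation; ρ = 0.5 and sphericity are assumed.

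- N = 28: λ = 0.0625 × 28 × 3 / 0.5 = 10.5, power 0.812.
- N = 26: λ = 0.0625 × 26 × 3 / 0.5 = 9.75, power 0.778.

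So 28 reproduces, as does the control target: 14/(1 − 0.30) = 20. The calculation is for equal arms.

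**2. Completers.** Applying 30% loss to both arms gives 39 × 0.7 = 27.3, taken as 27, and 20 × 0.7 = 14. Section 8.2 applies the allowance to controls only, so loss in the drumming arm is an assumption; step 5 varies it.

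**3. Standard error of the difference in mean change.** Write s_D and s_C for the SDs of change in the drumming and control arms.

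- Pooled: SE² = [(26·s_D² + 13·s_C²)/39] × (1/27 + 1/14)
- True: SE² = s_D²/27 + s_C²/14

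Controls 1.5 times as variable (s_D = 1, s_C = 1.5): pooled variance = (26 + 29.25)/39 = 1.417; pooled SE² = 1.417 × 0.1085 = 0.154; true SE² = 0.0370 + 0.1607 = 0.198; SE ratio = √(0.154/0.198) = 0.88.

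Drumming 1.5 times as variable: pooled variance = (58.5 + 13)/39 = 1.833; pooled SE² = 0.199; true SE² = 0.0833 + 0.0714 = 0.155; SE ratio = 1.13.

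At 14 v 14 the pooled SE² is [(s_D² + s_C²)/2] × 2/14, which equals the true value, so the ratio is 1 for any SDs.

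**4. Type I error at 27 v 14, nominal 5%.** The normal approximation is 2·[1 − Φ(1.96 × SE ratio)], with the unrounded ratio. The last two columns are simulated under the null, with normal data, three time points and compound symmetry.

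| Assumed SD | SE ratio | Normal approx. | Pooled week-10 contrast | Interaction F |
|---|---|---|---|---|
| Control 1.25× | 0.93 | 6.8% | 7.0% | 7.5% |
| Control 1.5× | 0.88 | 8.4% | 8.8% | 10% |
| Control 2× | 0.82 | 10.8% | 10.6% | 13% |
| Drumming 1.25× | 1.07 | 3.5% | 3.4% | 3.4% |
| Drumming 1.5× | 1.13 | 2.6% | 3.0% | 2.3% |
| Drumming 2× | 1.22 | 1.7% | 1.9% | 1.4% |

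Welch on the same week-10 change stays at about 5% in every row. Runs with ρ = 0.5 and ρ = 0.6 agree to about half a point. With equal SDs the pooled contrast and the interaction F are both at about 5%.

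**5. Other arm sizes** (pooled week-10 contrast, ρ = 0.5, 20,000 trials per cell; drumming/control SD ratios 0.8, 0.67, 0.5, then 1.25, 1.5, 2).

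- 39 v 20, no loss: 6.5%, 8.4%, 11.1%; then 3.5%, 2.8%, 1.8%.
- 39 v 14, loss in controls only: 7.4%, 10.3%, 14.7%; then 2.7%, 2.0%, 0.9%.
- 20 v 20: within about half a point of 5% throughout.

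The sensitivity therefore comes from the unequal arm sizes.

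**6. Price of Welch.** With equal SDs at 27 v 14 and an effect detected with power 0.805 by the pooled contrast, Welch has power 0.797, a loss of 0.8 points.

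**The case against.** The strongest reply is that handling unequal variance is routine content of an analysis plan, that no such plan is shown, and that the trigger, a real difference in variance, is nowhere in the protocol. The second part stands in full. A reader might infer that the p values are wrong, or that 5% is not the level of the test. The protocol does not support that: it gives no SDs, and with equal variances the planned test is valid. The first part stands only partly. Section 8.1 names a method and a threshold, and section 8.2 fixes arm sizes under which that method loses its usual protection. An unseen plan may already deal with this.

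A reader might also picture self-referred drumming participants against controls found by another route. Sections 6.1 and 6.4 describe self-referral without distinguishing arms, and section 5 gives one set of eligibility criteria. The documented difference is that controls already attend social activities. That makes equal variance of change an unsupported assumption; it does not show unequal variance.

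Two cautions on size also stand. Setting the interaction F beside a Welch test of one contrast overstates what Welch corrects; the fair comparison is pooled with Welch on the same contrast. And replacing the ANOVA by a single week-10 test would drop week 6, although section 3 sets out to compare 6 with 10 weeks and section 8.2 sizes the study on three time points.

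**Conclusion.** The point holds in conditional form. With 27 v 14 completers and SD ratios up to 2, the actual level of the pooled week-10 contrast ranges from about 1.9% to 10.6%, depending on which arm varies more. At a ratio of 1.25 either way it is about 3.4% to 7.0%, a moderate departure. Loss confined to controls widens the range. These figures rest on assumed SD ratios, normal data and, for the main table, equal proportional loss. The direction and size in this trial cannot be known from the protocol.

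The point concerns questionnaire outcomes, HADS first among them; the saliva markers have no control arm. Nor should an unequal-variance test be taken to make the between-arm comparison sound: confounding from non-random allocation is a separate and larger threat that it leaves in place. The change is still worth making, because it protects the primary test at little cost and settles the choice before the data are seen.

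**What to change.** In section 8.1, state that the between-arm planned simple contrasts on HADS, baseline to week 6 and baseline to week 10, take their p values and confidence intervals from an unequal-variance method. Name one in advance: Welch on change from baseline, or a baseline-adjusted model with HC3 standard errors. The figures above were worked out for Welch only. Keep the repeated-measures ANOVA as the overall group x time summary, so that all three time points stay in the analysis, and note that its F test remains sensitive to unequal variance.

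The cost is a short addition to 8.1 and about 1 point of power if the variances are equal. It needs no new data and no change to recruitment, and SPSS prints the Welch result beside the pooled one.
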